## Methods

### Aims

The primary aim of this study is to determine whether the creation and integration of at-risk asthma registers into primary care, as conceptualised in our ’At-Risk Registers Integrated into primary care to Stop Asthma crises’ (ARRISA) intervention, reduces asthma-related crisis events (A&E attendances, hospitalisations and deaths) for *at-risk patients* over a 12-month period compared to control practices. Our secondary aims are to assess outcomes (time to first crisis event, asthma control, all-cause admission or death) for *all* patients with asthma; and also to examine changes in the processes of asthma care (treatments, vaccinations, use of action plans or smoking cessation services, adherence to treatment) within practices. We also aim to assess whether this intervention is acceptable to healthcare professionals and patients and cost-effective from the perspective of the National Health Service (NHS). We will identify characteristics that influence uptake, integration and effectiveness of the intervention and explore causal mechanisms leading to changes in outcomes, including any unanticipated effects.

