**Methods:**

We are undertaking a pragmatic, two-arm, multicentre, cluster randomised controlled trial, plus health economic and process evaluation. We will randomise 270 primary care practices from throughout the UK covering over 10,000 registered patients with ‘at-risk asthma’ identified according to a validated algorithm. Staff in practices randomised to the intervention will complete two 45-min eLearning modules (an individually completed module giving background to ARRISA and a group-completed module to develop practice-wide pathways of care) plus a 30-min webinar with other practices. On completion of training at-risk patients’ records will be coded so that a flag appears whenever their record is accessed. Practices will receive a phone call at 4 weeks and a reminder video at 6 weeks and 6 months. Control practices will continue to provide usual care. We will extract anonymised routine patient data from primary care records (with linkage to secondary care data) to determine the percentage of at-risk patients with an asthma-related crisis event (accident and emergency attendances, hospitalisations and deaths) after 12 months (primary outcome). We will also capture the time to crisis event, all-cause hospitalisations, asthma control and any changes in practice asthma management for at-risk and all patients with asthma. Cost-effectiveness analysis and mixed-methods process evaluations will also be conducted.

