#### Secondary outcomes

The time to first, and rate of, asthma-related crisis event(s) (defined as above) for at-risk patientsThe percentage of all registered asthma patients with an asthma-related crisis event, their rate of, and time to, first asthma-related crisis event(s) (as above)The percentage of at-risk and all registered asthma patients with good control defined as answering ‘no’ to all of the RCP3Qs [29]The percentage of at-risk and all registered asthma patients requiring a hospital admission or dying for any reasonThe number of the following (per patient per year) for both at-risk and all registered asthma patients:

(a) short-acting bronchodilator prescriptions issued

(b) prescriptions of systemic corticosteroids for asthma attacks and antibiotic-treated lower respiratory tract infections

(c) modifications of the prescription of asthma-related medications to align more closely with current guidelines (e.g. increased use of inhaled corticosteroids)

(d) records of written personalised asthma action plans and patient self-monitoring with peak flow diaries

(e) inhaler technique assessments recorded

(f) smoking cessation advice or smoking cessation medications given

(g) flu vaccinations

(h) ‘did not attends’ at primary and secondary care routine appointments

(i) adherence to medication determined from validated computer-based calculations using prescription data

Health economic outcomes6.The estimated (per patient) mean incremental cost of the at-risk register compared with usual care7.The incremental effect of the at-risk register, in terms of the estimated (per patient) mean difference (between arms) in the number of asthma crisis events

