### Data collection

#### Baseline characteristics and outcome data

All practices expressing interest in the study are asked to complete an initial questionnaire to provide basic data on practice characteristics.

All participating practices must agree to share their practice EHRs with Optimum Patient Care (Cambridge, UK). Obtaining data in this way not only permits linkage to different databases (practice EHRs, Office for National Statistics (ONS), Hospital Episode Statistics (HES)), but also permits data capture without burdening the practice or patients. All practices (control and intervention) are asked to insert a specific Read code that cannot be readily removed by practice staff into the EHRs of at-risk asthma patients to denote inclusion in this study. This will be used by data managers and statisticians to identify these patients and distinguish their data from other patients with active asthma in the practice. For the purposes of data collection, active asthma is defined using the QOF criterion [27]: Read code for asthma diagnosis plus asthma therapy in the past year, excluding those coded as asthma resolved but not excluding QOF exception codes. At the end of the study, data extractions will be obtained for all patients with asthma in the practice containing data for the 12 months before randomisation and the 12 months following the activation of the flag in the intervention practices. The mean time from randomisation to activation of the flag will be calculated for all intervention practices, and data collection will be captured for 12 months from this time after randomisation in the control practices. For clinical event data and for patients’ demographic and other characteristics (weight, height, smoking status, etc.) the last recorded value will be obtained.

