### Analysis

#### Effectiveness analyses

The primary comparison of treatment arms at 12 months will be based on the intention-to-treat (ITT) principle including all patients initially identified with ‘at-risk’ asthma using the risk algorithm. The primary outcome will be analysed on an individual-level using a logistic regression model with random effects to allow for the clustering of patients by practice and fixed effect for the factors included in the stratification, i.e. practice software and practice diploma-trained nurse. A similar model will be used for the number of events, based on a Poisson regression model with random and fixed effects, and the time until the first event. Secondary outcomes will be analysed in a similar fashion, which is to say that the binary outcomes will be analysed using logistic regression models and all count outcomes using Poisson regression. All model assumptions will be assessed using appropriate techniques and for Poisson regression models over dispersion will also be checked.

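### The stated models for the process-of-care outcomes omit the prior-year values that the trial extracts, which costs avoidable precision on an aim framed as change in care

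*Protocol article*

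**What the plan says.** All references are to the protocol article.

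- **Aims** sets a secondary aim "to examine changes in the processes of asthma care (treatments, vaccinations, use of action plans or smoking cessation services, adherence to treatment) within practices". The **abstract (Methods)** says the trial will capture "any changes in practice asthma management for at-risk and all patients with asthma".
- **Secondary outcomes** defines the process and prescribing measures, items (a) to (i), as the "number of the following (per patient per year) for both at-risk and all registered asthma patients". Two items differ in kind: (c) is "modifications of the prescription of asthma-related medications to align more closely with current guidelines", and (i) is "adherence to medication determined from validated computer-based calculations using prescription data".
- **Baseline characteristics and outcome data** says the extract takes in everyone with asthma at each site. Its time span is described as "containing data for the 12 months before randomisation and the 12 months following the activation of the flag in the intervention practices". Control practices get a matching follow-up window.
- **Effectiveness analyses** states the primary model as follows: "logistic regression model with random effects to allow for the clustering of patients by practice and fixed effect for the factors included in the stratification". Those factors are software type and whether a nurse holds the asthma diploma. It continues: "Secondary outcomes will be analysed in a similar fashion", with logistic models for binary outcomes and Poisson models for counts.

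No prior-year value, period term or other baseline covariate is named. The article states no analytic use of the prior-year outcome data.

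**The concern.** The aim speaks of change, the data to measure each practice's starting point are collected, and the stated model does not use them. For measures such as reliever prescriptions, inhaler checks or written action plans, a practice's own routine plausibly persists from one year to the next. It is known before allocation, so adjusting for it is safe. If it is left out, stable differences between practices widen the standard error of the arm contrast, and any chance imbalance in those habits passes into the estimate.

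Two uses of these outcomes make precision matter. They are the main quantitative evidence on whether care altered, and the process evaluation treats them as intermediaries on the causal path. The Background also hypothesises that the care of asthma patients not at risk will not suffer. An avoidably wide interval around no difference is easily misread as support for that.

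**Working it through.** **1. The plan's own figure.** Sample size gives 8204 patients from 235 practices for 7% versus 5%, 90% power, cluster size 35 and ICC 0.01. I assume two-sided alpha 0.05, which is not stated. The two-proportion formula with continuity correction gives 3061 per arm. The design effect is 1 + 34 × 0.01 = 1.34. Then 2 × 3061 × 1.34 = 8203, and 8203 / 35 = 234.4, rounded up to 235. The figure reproduces. It concerns the primary outcome only and neither supports nor weakens this point.

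**2. Formula for the gain.** For a comparison of practice means, adjusting for the baseline mean multiplies the variance of the arm contrast by 1 − r², where

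r = [m × ICC × CAC + (1 − ICC) × IAC] / [1 + (m − 1) × ICC].

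Here m is patients per practice, CAC is the year-to-year correlation of the practice effects, and IAC is the same for a patient within a practice. This is a linear approximation to the Poisson mixed model.

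**3. Inputs.** m = 35 is from Sample size. ICC, CAC and IAC for process measures appear nowhere in the article. I assume ICC 0.01 to 0.20, CAC 0.5 to 0.9 and IAC 0 to 0.5.

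**4. Results.** Low is CAC 0.5 with IAC 0. High is CAC 0.9 with IAC 0.5. The between-practice share of the variance of a practice mean is m × ICC / [1 + (m − 1) × ICC].

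| ICC | Between-practice share | r, low | r, high | 1 − r², low to high | Variance saved |
|---|---|---|---|---|---|
| 0.01 | 0.35/1.34 = 26% | 0.131 | 0.604 | 0.983 to 0.635 | 1.7% to 36.5% |
| 0.05 | 1.75/2.70 = 65% | 0.324 | 0.759 | 0.895 to 0.424 | 10.5% to 57.6% |
| 0.10 | 3.50/4.40 = 80% | 0.398 | 0.818 | 0.842 to 0.331 | 15.8% to 66.9% |
| 0.20 | 7.00/7.80 = 90% | 0.449 | 0.859 | 0.799 to 0.262 | 20.1% to 73.8% |

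Example, first row, high: (35 × 0.01 × 0.9 + 0.99 × 0.5) / 1.34 = 0.810 / 1.34 = 0.604, and 1 − 0.604² = 0.635.

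**5. In terms of power.** Take a narrower and more favourable set: ICC 0.02 to 0.20, CAC 0.6 to 0.8, IAC 0.3 to 0.6.
- Low end: r = (0.42 + 0.294) / 1.68 = 0.42, SE ratio √(1 − r²) = 0.91.
- High end: r = (5.6 + 0.48) / 7.8 = 0.78, SE ratio 0.63.
- An effect with 80% power unadjusted would have power Φ(2.80 / SE ratio − 1.96), which is about 87% to 99%.
- For all registered asthma patients, with an assumed 300 per practice, the SE ratio is 0.83 to 0.60.

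**6. Why not a change score.** A raw change score has variance factor 2(1 − r). This exceeds 1, and so is worse than ignoring baseline, whenever r < 0.5. At ICC 0.01, CAC 0.5 and IAC 0 it is 2 × (1 − 0.131) = 1.74. It is never better than adjustment, since 2(1 − r) − (1 − r²) = (1 − r)² ≥ 0.

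**The case against.** - **The analysis plan may add baseline covariates.** This is true, and a condensed article need not list everything. But the article is not silent on adjustment. It names the model terms and carries them over to the secondary outcomes, without the one its own extract supplies. The point is limited to that stated model.
- **The aim is answered.** A reader might infer that a post-period comparison cannot address an aim about change. The document does not support that. Under randomisation the arm contrast validly estimates the change in care caused by the intervention, and the wording in Aims does not commit the trial to a before-after estimand. Baseline adjustment targets essentially the same effect, more precisely. This objection stands.
- **Not every process outcome is a post-period count.** Item (c) itself counts modifications, and item (i) is a calculated adherence measure. Under Process evaluation data, both arms are asked about major changes in asthma management policy. This stands too, and the fix is limited accordingly.
- **Practice habits are modelled.** A reader might say they are left as unexplained error. In fact they enter the practice random effect and, in part, the software and nurse terms. That is correct, but they still widen the standard error of a contrast made between practices.
- **The size is assumed.** This stands. At-risk patients are selected partly on exacerbation history and prescribing data (Intervention), which could weaken patient-level correlation. The table therefore runs down to IAC 0, where the gain at ICC 0.01 can be negligible.

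**Conclusion.** The point holds as a matter of efficiency in secondary outcomes. The article frames an aim as change in care and collects the prior year in both arms, yet states models without a baseline term. There is no bias, no contradiction that defeats the aim, and no effect on the primary analysis or the sample size. The costs are avoidable imprecision and exposure to chance imbalance in standing practice habits.

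The size cannot be fixed from the document. With 35 patients per practice, CAC 0.5 to 0.9 and IAC 0 to 0.5, all but the cluster size assumed, the variance saving runs from near nothing (1.7%) at ICC 0.01 with low correlations to 73.8% at ICC 0.20 with high ones. The gain is small only when both the ICC and the year-to-year correlations are low. Since the data are already in hand, the change is worth making even though its benefit is uncertain.

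**What to change.** In Effectiveness analyses, state the following for process and prescribing outcomes that have a prior-year value, for example items (a), (b), (d), (e) and (g):

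1. The model also includes the patient's value of the same measure in the 12 months before randomisation, and the practice mean of that value.
2. The reported effect is the baseline-adjusted ratio between arms.
3. Raw change scores are not used. Besides the variance penalty shown above, selection on past exacerbations and prescribing means that a simple before-after figure would include regression to the mean.
4. For a patient with less than 12 months of prior record, the practice mean is used with a missing indicator.

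The cost is a short addition to the text and minor programming on data already in the extract. The one small downside is the handling of incomplete prior records. Rewording the aim as a comparison between arms would tidy the text but would not recover the precision.

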### Trial design

This is a two-arm, pragmatic, multicentre, cluster randomised controlled trial plus health economic and process evaluation comparing usual care (control) to a complex, primary care practice-level intervention comprising: (1) creation of an asthma at-risk register, (2) online eLearning training for practice staff, (3) Computerised Decision Support System (CDSS) involving flagging of at-risk patients’ records to prompt agreed actions and (4) ongoing practice support. The intervention targets all healthcare professionals and reception staff within practices. The trial outline is shown in Fig. 1 and the schedule of enrolment, interventions and assessments is shown in Fig. 2. The trial protocol (v1.3, dated 23 March 2018) is based on the Standard Protocol Items: Recommendations for Interventional Trials (SPIRIT) 2013 Statement for protocols of clinical trials (see Additional file 1).

**Fig. 1 Fig1:**
[figure not shown]
ARRISA-UK trial outline

**Fig. 2 Fig2:**
[figure not shown]
ARRISA-UK schedule of enrolment, interventions and assessments

Routinely available data from patient records on outcomes, processes of care and healthcare use will be captured anonymously, without the involvement of the practice, at the end of the 12-month study period. Additional resource use data, for the purposes of economic evaluation, will be captured during the online training, post training and 12-month questionnaires. Data from a baseline practice demographic survey, the training software, questionnaires completed post training and at 12 months, plus focus groups and individual interviews undertaken with a sub-sample of practice staff and patients towards the end of the study, including those from the whole asthma population and those with at-risk asthma in the intervention and control groups (see below), will contribute to the process evaluation. This will take a mixed-methods sequential explanatory approach to exploring implementation, mechanisms and contextual influences on the intervention.

### Setting

The setting is primary care practices within the UK, with health economic analysis from the perspective of the NHS.

## Participants

### Clusters – Primary care practices

#### Recruitment

Primary care practices are being identified via the National Institute for Health Research (NIHR) Clinical Research Networks (CRN), Health and Care Research Wales, the Scottish Primary Care Research Network (SPCRN) and respiratory charities, societies and networks. The regions involved are: East Midlands, Eastern, Greater Manchester, Kent Surrey and Sussex, North East and North Cumbria, North Thames, North West Coast, North West London, South West Peninsula, Thames Valley and South Midlands, Wessex, West Midlands, West of England, Yorkshire and Humber in England, plus Scotland and Wales. Practices are selected by purposive sampling to ensure adequate representation from the devolved nations, from urban versus rural areas, and using different general practitioner (GP) software systems. All practices complete an online practice questionnaire as part of the recruitment process to check eligibility before randomisation and to provide stratification information and demographic data.

#### Inclusion criteria

Primary care practices in the UK.

### Individual patients

Patients at recruited practices are included in the study if they have at-risk asthma as determined by our algorithm applied to routinely available primary care data forming the ‘original register’. Practice staff may add or remove patients from the register (see below), but the primary analysis will be conducted using data from all patients on the original register without additions or withdrawals. In addition, data from all patients with asthma defined on the basis of being on the practice asthma register will be included for the purpose of examining secondary outcomes.

Patients will be excluded if they have refused for their anonymous data to be used in research or are terminally ill and receiving palliative care. Patients have the right to refuse access to their data at any point until the conclusion of the data extraction.

### Process evaluation

#### Inclusion

As well as cluster- and patient-level data as above, for the purposes of the process evaluation selected practice staff and patients at participating practices will be approached to be involved in focus groups and/or qualitative interviews.

#### Exclusion

Individuals of under 16 years of age, unable to communicate in English or give informed consent will be excluded from focus groups and interviews.

### Intervention

This is a practice-wide (cluster-level) complex intervention comprising four main components:

1. Establishment of a practice at-risk asthma register:

We have developed and validated an algorithm, using routinely collected primary care data, for identifying those patients most at risk of attending A&E, being admitted to hospital or dying from an asthma attack. Factors in the algorithm include previous exacerbation history, coding for anxiety or depression, smoking history and prescribing data and laboratory results. Automated electronic searches identify patients with at-risk asthma from practice-based data using this algorithm. This is a two-stage process with the initial generation of an anonymised list and then coding to provide the names and details of the patients. Programmes and instructions for searches, with frequently asked questions, for the specific computer software programme of each practice will be sent to the information technology (IT) lead at the practice by email or compact disc (CD).

A representative (usually asthma GP lead or asthma nurse) at each intervention practice receives a document by email which explains ‘at-risk asthma’ and gives instructions on how to modify the list of patients with their records flagged (see CDSS below). GPs and asthma nurses are able to review the computer-generated list of at-risk patients, and exceptionally, with documented justification of the change, delete any who should not be on the list (e.g. receiving palliative care) and identify any other ‘at-risk’ patients known to them. They may modify the list, as above, for the duration of the study although the primary analysis will be based on data from patients included in the original register prior to modifications

2.  Practice-wide, online training (eLearning)

We have developed an innovative multi-component practice-wide intervention based on the material delivered in the face-to-face training developed for the prior regional study [22], but incorporating eLearning modules similar to those that have been previously shown to be successful in changing clinician behaviours [26]. Each practice is asked to nominate a representative from each staff discipline, e.g. nurse, GP, pharmacist (in dispensing practices) and receptionist (referred to collectively hereafter as ‘practice representatives’). A dedicated member of the practice staff (generally the practice asthma nurse) is then charged with championing the intervention at the practice (referred to hereafter as the practice champion) and ensuring dissemination via the practice representatives to maximise uptake. Practice representatives receive a document describing the purpose of the training and providing log-in details to the eLearning training resource. The eLearning modules have been developed in conjunction with Healthcare-Learning (www.healthcare-learning.com). They are hosted on the HealthCare-Learning secure website with links from the Asthma UK Centre for Applied Research website (www.aukcar.ac.uk). The main purpose of the education is to advise all practice staff on actions to take when presented with the electronic flag (see CDSS below) on the EHRs of an at-risk patient. It comprises two eLearning modules and a webinar:

(a) An individually completed module

This provides information on the national and patient perspectives of managing at-risk asthma, NRAD results [10], findings from the studies that were precursors to the ARRISA-UK study [21, 22], the flags to be added to patient records and discipline-specific training as to suggested actions to be undertaken on seeing the flag. The training uses a case scenario to highlight the possible benefits of the intervention and self-assessments to permit active learning and self-reflection. This module is to be undertaken by the practice champion and representatives and takes up to 45 min to complete.

(b) A practice-representative team completed module

This module is organised and chaired by the practice champion and attended by all of the practice representatives. The purpose of this module is to permit representatives of the practice team to collectively reflect on the material contained in the first module and encourage practice staff to agree on and document how the intervention will be implemented in their practice via a practice ‘action plan’. This covers the wording of the flag, proposed actions of each staff discipline in response to the flag, plans for including information in staff induction and disseminating to all staff, stance on informing patients about their at-risk status and a method for communicating with out-of-hours services. This module takes up to 45 min to complete

(c) A webinar

Ideally, within 8 weeks of completion of the second module, the practice representatives are asked to dial into a 30-min ‘webinar’ (online discussion) which reviews the learning objectives and outcome from the modules. It permits discussion within and between practices (in groups of between two and eight practices) participating in the study, allowing them to share experiences and ideas, and refine their practice implementation and dissemination plans accordingly. The webinars are being delivered by the GP lead who originally implemented an at-risk asthma register at his practice [21], developed and led the face-to-face training in the prior study [22], and was involved in developing the eLearning modules

